#### **Introduction:**

This prospective pilot study examines the effectiveness of care and patient satisfaction in Europe's first specialized outpatient clinic that focuses on the influence of nutrition on mental and psychosomatic health. In addition, other specialized outpatient clinics of our department, in particular the clinic for psychocardiology and for psychohepatology, will be evaluated. The aim of the study is to document and assess changes in patients' subjective perception of stress and in their mental health before and during care over a period of one year. Furthermore, potential associations between psychological well-being and specific nutrition-related as well as physiological parameters will be investigated.

#### **Methods:**

Standardized psychological questionnaires will be used to assess participants' stress levels, resilience, somatic symptoms and quality of life. Patient satisfaction will also be recorded using adapted questions that are answered regularly over the course of the study period. To identify possible physiological correlates, blood samples will be taken as part of routine laboratory work and analyzed for relevant markers such as inflammatory factors (e.g., CRP). Data collection takes place at baseline and at three-month intervals throughout the study period.

#### **Expected results:**

A reduction in subjective stress perception and an improvement in psychological well-being as well as quality of life are expected. Positive changes in physiological parameters, particularly inflammatory markers, are also anticipated, suggesting a supportive effect of nutrition-based interventions on psychosomatic health.

#### **Discussion:**

The results of this pilot study are intended to provide insights into the effectiveness of nutrition-based and general interventions in psychosomatics and to highlight potential areas

for optimizing patient care. The study will serve as a basis for further research and could help to further establish the concept of Nutritional Psychiatry and Nutritional Psychosomatics as innovative treatment approaches in Europe.

### Scientific Background

Mental illnesses and psychosomatic complaints are among the most common and burdensome health problems worldwide. However, the classical therapeutic methods—consisting of psychotherapy and pharmacological treatment—are in many cases neither sufficiently curative nor preventive. Despite intensive interventions, more than 40% of patients do not respond adequately to therapy (Maes et al., 2009), and around 20–30% remain treatment-resistant and continue to suffer from distressing symptoms such as sleep disturbances, chronic pain and fatigue (Rush et al., 2006). In addition, there is a rising incidence of such disorders (GBD, 2019). These gaps in treatment success and the insufficient preventive options underline the need for new treatment approaches that more strongly integrate biological, psychological and social factors in the sense of the bio-psycho-social model.

An innovative approach in psychosomatic medicine and psychiatry is “Nutritional Psychiatry.” This emerging discipline explores the relationship between nutrition, mental health and physical symptoms and suggests that targeted nutrition-based interventions can improve mental and physical resilience. Research findings in nutritional psychiatry show that the interactions between body and psyche are strongly influenced by nutrition—particularly via the so-called gut-brain axis. This bidirectional connection regulates communication between the central nervous system and the gut microbiome and plays a central role in the regulation of mood and stress (Mörkl et al., 2019).

An imbalance in the gut microbiome, caused by an unbalanced diet, can trigger inflammation and dysfunctions in neurotransmitter production (Safadi et al., 2022). These mechanisms demonstrably contribute to the development of mental and psychosomatic disorders, for example by impairing the serotonin system, the majority of which (approx. 90%) is produced in the gut and substantially influences mood. For instance, the serotonin precursor tryptophan is reduced by inflammatory processes, thereby impairing serotonin production. Studies show that targeted dietary intervention can restore microbiome balance and reduce chronic inflammatory processes that are frequently associated with depression, burnout and stress-related disorders (Berding et al., 2023).

An anti-inflammatory dietary pattern, such as the Mediterranean diet, which is rich in omega-3 fatty acids, antioxidants and fiber, has proven particularly beneficial for mental health. It is not only associated with a lower risk of depression but also has preventive effects against

physical symptoms such as chronic pain and inflammation, which often occur in psychosomatic disorders (Jacka et al., 2017). These findings suggest that a nutrition-based intervention model could broaden psychosomatic treatment by specifically promoting a more comprehensive balance between body and mind, thereby supporting recovery and resilience. Against this background, the Specialized Outpatient Clinic for Psychosomatics and Nutritional Psychosomatics at LKH Graz offers a new approach to integrating individually tailored interventions that consider both nutrition and other health-promoting factors into psychiatric and psychosomatic treatment. The clinic follows a personalized treatment concept tailored to the needs of the patients and oriented toward salutogenesis. The aim is not only to alleviate symptoms but also to promote patients' healthy capacities and strengthen their resilience.

This prospective pilot study will investigate how targeted, personalized dietary interventions affect mental and physical symptoms—particularly subjective stress perception—in patients suffering from mental and psychosomatic complaints. This will generate new insights into the practical application of Nutritional Psychiatry and establish important foundations for future integrative therapeutic approaches that address body and mind together and enable a sustainable improvement in quality of life and health.

Within the Clinical Department of Medical Psychology, Psychosomatics and Psychotherapy at the LKH University Hospital Graz, further specialized psychosomatic outpatient clinics have been established to address the growing need for integrated care in somatic specialties: the outpatient clinic for psychocardiology and the clinic for psychohepatological and gastroenterological diseases. Psychocardiology focuses on patients with cardiovascular diseases such as myocardial infarction, heart failure or cardiac arrhythmias, which are often accompanied by psychological burdens such as anxiety disorders, depression or adjustment difficulties. Psychosocial factors, such as chronic stress or lifestyle problems (e.g., lack of exercise, inadequate diet), can also contribute to disease development or negatively influence its course. In this specialized clinic, which takes place every Tuesday in close cooperation with the Department of Cardiology, patients receive multidisciplinary care in the context of diagnostic, psychotherapeutic and educational measures.

The clinic for psychohepatology and psychogastroenterology is aimed at people with chronic gastrointestinal or liver diseases, particularly those with increased psychological stress potential—for example due to alcohol dependence, inflammatory bowel disease, non-alcoholic fatty liver disease or liver cirrhosis. Psychological comorbidities such as depression, anxiety disorders or maladaptive illness processing are common in this population and are associated with reduced adherence and quality of life. The treatment program includes psychological diagnostics, individual and group therapy, lifestyle counseling and motivational interviewing. Both clinics are based on an integrated care model that systematically links psychological, social and somatic aspects and thereby specifically treats patients whose psychosomatic care is often inadequately represented in standard care. High utilization and feedback from the cooperating clinical departments confirm the need for these specialized, interdisciplinary services.

The aim of the present investigation is to gain new insights into the practical implementation of integrated psychosomatic care in cardiology as well as in gastroenterology and hepatology. The intention is to establish central foundations for future therapeutic approaches that systematically address mental and physical health together. By evaluating these specialized clinics, a contribution is to be made to the development of sustainable, holistic treatment forms that improve patients' quality of life and overall health in the long term.

## **Objectives and Hypotheses**

This pilot study aims to conduct an initial evaluation of the Specialized Outpatient Clinic for Nutrition and Mental Health and to evaluate other specialized clinics with innovative care concepts within our department. Initial data on treatment outcomes and patient satisfaction will be collected and analyzed. The findings will be used to identify and implement targeted optimization potential in patient care.

The central research question of this study is: Can continuous care in Europe's first Specialized Outpatient Clinic for Nutrition and Mental Health achieve a statistically significant reduction in stress levels in patients with psychosomatic disorders after one year of treatment? Is there also an influence on stress levels in our other specialized outpatient clinics?

As part of the individually tailored interventions aimed at nutrient supply, nutrition, the gut-brain axis and relationship-based medicine, we expect a significant reduction in patients' stress symptoms.

## **Hypotheses**

The null hypothesis of the study is: There is no statistically significant reduction in stress levels in patients with psychosomatic disorders after one year of treatment in the specialized outpatient clinics of our department.

The alternative hypothesis is: After one year of treatment in the Specialized Outpatient Clinic for Nutrition and Mental Health, there is a statistically significant reduction in stress levels in patients with psychosomatic disorders in the specialized outpatient clinics of our department.

## **Study Design**

This study will be conducted at the Clinical Department of Medical Psychology, Psychosomatics and Psychotherapy as a single-center, prospective pilot study.

Patients will be referred by private psychiatrists and/or general practitioners, as well as by colleagues from internal medicine (cardiology/gastroenterology/hepatology). Recruitment takes place during the initial consultation in the specialized outpatient clinic. Patients are informed about the possibility of participation when registering at the clinic desk and receive the information sheet so that they can read it independently before the consultation. During the initial consultation, patients are again comprehensively informed about the study by the physicians. Participation is voluntary and requires written informed consent.

Participants will complete questionnaires at baseline and subsequently at three-month intervals for one year. Laboratory tests will be performed during regular follow-up appointments in the clinic, which also take place every three months. The questionnaires will be completed online using the EvaSys system. A link will be sent to participants by email.

## **Baseline Procedure**

After the initial consultation, participants receive an email with a link to the baseline questionnaires, which they should complete within one week. The following assessments will be conducted:

- Assessment of health literacy

- Baseline general patient satisfaction
- NutriMental Screener
- Perceived Stress Scale (PSS10)
- SF-12
- BRS-D (resilience)
- Somatic Symptom Scale
- EQ-5D-5L
- Food Frequency Items
- OPD-SFK

### **Follow-Up Procedure**

At three-month intervals, participants will again receive an email with a link to the following assessments:

- Assessment of health literacy
- Follow-up general patient satisfaction
- Perceived Stress Scale (PSS10)
- SF-12
- BRS-D (resilience)
- Somatic Symptom Scale
- EQ-5D-5L
- Food Frequency Items
- OPD-SFK

### **Inclusion and Exclusion Criteria**

Inclusion criteria: Informed consent, new patient of the specialized outpatient clinics, age between 18 and 65, German language; having the means and being able to access and complete the questionnaires online via email.

Exclusion criteria: Lack of consent or capacity to consent, dementia (Mini-Mental Score < 20), pronounced dependence on alcohol and/or psychotropic substances (benzodiazepines, morphine), severe physical, neurological and motor impairments that make answering the questionnaires impossible, no possibility or ability to access and complete the questionnaires online, tumor diseases, severe autoimmune diseases or immunosuppression.

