#### **Secondary Outcome Measures**

- Scores of the questionnaires on resilience, quality of life, somatic symptoms, personality structure
- Dietary history: Food Frequency Items
- Patient satisfaction
- Subjective health literacy
- Blood parameters: differential blood count, CRP, IL-6, fasting blood glucose, HOMA index, cholesterol, HDL, LDL, triglycerides, ALT, AST, GGT, creatinine, urea, electrolytes, uric

acid, vitamin D, ferritin, homocysteine, vitamin B12

- Demographic data

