### Standard Laboratory

Blood samples will be taken at baseline and then every three months during the regular follow-up appointments by staff in the specialized outpatient clinics. A total of approx. 45 ml of blood (approx. 3 tablespoons) will be drawn and analyzed in a routine laboratory.

The following routine parameters are of particular interest for this study: differential blood count, CRP, IL-6, fasting blood glucose, HOMA index, cholesterol, HDL, LDL, triglycerides, ALT, AST, GGT, creatinine, urea, electrolytes, uric acid, vitamin D, ferritin, homocysteine, vitamin B12

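### CRP and IL-6 could fall from baseline through recovery alone if some patients are first sampled soon after an acute event; recording acute illness at each draw is a cheap safeguard

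*Protocol*

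**What the plan says.** Under Inclusion and Exclusion Criteria, the inclusion list opens with "Informed consent, new patient of the specialized outpatient clinics, age between 18 and 65, German language". The exclusions that bear on inflammatory markers are "tumor diseases, severe autoimmune diseases or immunosuppression". Neither list mentions time since an acute event, clinical stability or current acute illness.

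The Scientific Background says "Psychocardiology focuses on patients with cardiovascular diseases such as myocardial infarction, heart failure or cardiac arrhythmias". The liver and gastroenterology clinic takes patients with, among other conditions, inflammatory bowel disease and cirrhosis. Under Study Design, referral comes from psychiatrists and general practitioners "as well as by colleagues from internal medicine (cardiology/gastroenterology/hepatology").

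The secondary outcomes include "Blood parameters: differential blood count, CRP, IL-6, fasting blood glucose, HOMA index", and ferritin is also listed. Under Standard Laboratory, "Blood samples will be taken at baseline and then every three months during the regular follow-up appointments". The clinical data listed under Questionnaires include medication and chronic organic disease, but not the date of a recent event or illness at the time of the draw.

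The Statistics section plans paired t-tests and repeated-measures ANOVA for change over time. No control group is described. The expected-results section states: "Positive changes in physiological parameters, particularly inflammatory markers, are also anticipated, suggesting a supportive effect of nutrition-based interventions on psychosomatic health".

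**The concern.** CRP, IL-6 and ferritin rise in acute illness and fall as it resolves. Chance infections strike baseline and follow-up draws about equally and largely cancel in a before-after comparison. An acute event shortly before a patient's first visit does not cancel. It raises only the baseline value, so recovery pushes the change downward, which is the direction the protocol expects. An uncontrolled within-patient test cannot separate that fall from an effect of care.

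The planned interpretation adds to the problem. Psychocardiology, the clinic most open to this bias, is described as offering diagnosis, psychotherapy and patient education, not nutrition-based care. Yet the expected-results statement is not limited to the nutrition clinic. At stake is what the study may say about inflammatory markers. The primary outcome, perceived stress, is not touched by this point.

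**Working it through.** **Inputs from the protocol (Considerations on Sample Size).** Nutrition clinic: 10 per month × 12 = 120, × 0.70 = 84 participants, which reproduces the stated figure. Psychocardiology: about 150 slots ÷ 3 to 2.5 contacts = 50 to 60 new patients a year. Liver clinic: 46 days × 1 to 2 = 46 to 92 first contacts. The 70% uptake is stated only for the nutrition clinic.

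**Assumptions, none of them in the protocol.** A share of 10 to 20% of psychocardiology patients is first sampled soon after an acute event. Each of them has a transient CRP excess D of 10 to 40 mg/L that has resolved by follow-up. No patient has a true treatment effect. The SD of change from other causes, s, is 3 or 10 mg/L.

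**Formula.** With p the affected share of the n patients analysed: mean fall = pD; SD = √(p(1−p)D² + s²); t = mean ÷ (SD/√n).

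Example, psychocardiology at the midpoint n = 55, p = 0.10, D = 40, s = 3: mean = 4.0 mg/L; SD = √(0.09 × 1600 + 9) = 12.4; t = 4.0 ÷ (12.4/7.42) = 2.4.

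For the pooled rows, the affected count and the total use the same psychocardiology figure:
- Low case: 10% of 50 = 5, of 84 + 50 + 92 = 226.
- High case: 20% of 60 = 12, of 84 + 60 + 46 = 190.

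| Scenario | D=10, s=3 | D=40, s=3 | D=10, s=10 | D=40, s=10 |
|---|---|---|---|---|
| Psychocardiology, n=55, 10% | 1.75 | 2.4 | 0.7 | 1.9 |
| Psychocardiology, n=55, 20% | 3.0 | 3.6 | 1.4 | 3.1 |
| All clinics, 5 of 226 | 1.0 | 2.0 | 0.3 | 1.1 |
| All clinics, 12 of 190 | 2.3 | 3.4 | 0.8 | 2.5 |

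The two-sided 5% critical value is about 2.0 throughout.

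**70% uptake in every clinic (s = 3).** Psychocardiology n = 0.7 × 55 = 38.5: t is 1.5 to 2.0 at 10% and 2.5 to 3.0 at 20% (D = 10 to 40). Pooled low case, 3.5 of 84 + 35 + 64.4 = 183.4: t is 0.8 to 1.7. Pooled high case, 8.4 of 84 + 42 + 32.2 = 158.2: t is 1.8 to 2.8.

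**Rank test.** Suppose the k affected patients show the k largest changes, all falls, and the others are symmetric about zero. The expected Wilcoxon sum for falls is then k(n − (k−1)/2) + (n−k)(n−k+1)/4. The null mean is n(n+1)/4 and the null SD is √(n(n+1)(2n+1)/24).
- 5 of 55: 265 + 637.5 − 770 = 132.5; SD 119.4; z = 1.1.
- 11 of 55: 550 + 495 − 770 = 275; SD 119.4; z = 2.3.
- 5 of 226: 1120 + 12265.5 − 12825.5 = 560; SD 984; z = 0.6.
- 12 of 190: 2214 + 7965.5 − 9072.5 = 1107; SD 759; z = 1.5.

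**Check on a standardised scale.** A simulation of 20,000 paired t-tests per setting used recovery falls of 0.5 to 1.5 SD and no treatment effect. The nominal chance of a false significant fall is 2.5%. Within psychocardiology (n = 35 to 42) it was about 5 to 12% with a 10% affected share and 8 to 32% with 20%. Pooled (n about 151 to 190), it was about 4 to 6% and 5 to 12%.

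**The case against.** The strongest objection is that the mechanism rests on a timing the protocol never gives. A reader might infer that the acute event is often the reason for referral, so that raised values gather at baseline and are gone by month 3. The Scientific Background says only that the clinic sees "patients with cardiovascular diseases such as myocardial infarction, heart failure or cardiac arrhythmias" who also carry psychological burdens, and Study Design says only who refers them. Neither gives the time from event to referral or to first draw. This part of the objection stands: the bias is conditional and its frequency unknown.

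A reader might also infer that a few recently ill patients will produce a significant fall. The table does not support that as a general statement. Several settings give t below 2.0, pooling dilutes the effect, and a rank test shrinks it. The protocol plans distribution checks and does not rule out a rank test. The shrinkage is not complete, however: at 20% affected in psychocardiology, z is still about 2.3.

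Nor does the protocol say that the exclusions were chosen to protect marker analyses, so this is not a failure of their stated purpose. Open eligibility suits an evaluation of routine clinics, and the exclusion of severe autoimmune disease may already remove some patients with inflammatory bowel disease.

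Finally, handling flagged draws could be left to a statistical analysis plan, the markers are secondary in a pilot, and the expected-results statement is cautiously worded. All true, but an analysis plan cannot condition on an illness flag that was never collected. That makes the data capture a protocol matter.

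**Conclusion.** The point holds as a low-cost improvement for secondary outcomes. The protocol admits patients in whom recent acute illness is possible, records nothing at the draw that would identify them, tests change without a control, and would credit a fall to nutrition-based interventions even in clinics not described that way.

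The direction of the bias is clear if such patients exist; its size cannot be determined from the protocol. Under the stated assumptions with s = 3 mg/L, t is about 1.8 to 3.6 within psychocardiology and 1.0 to 3.4 pooled. The values are lower with a larger SD, 70% uptake everywhere or a rank test. The result therefore runs from negligible to clearly significant, and psychocardiology is the most exposed of the settings examined.

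The documents do not support a claim that a false positive is likely, that the eligibility criteria must change, or that the perceived-stress result is affected.

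**What to change.** 1. At each routine draw, record whether there was an acute infection, an acute cardiac event or an unplanned hospital stay within one prespecified preceding period.
2. Analyse change in CRP, IL-6 and ferritin by clinic on unflagged draws. Apply the rule identically at baseline and follow-up, and report the analysis of all draws beside it.
3. In the expected-results section, limit the nutrition interpretation of inflammatory markers to the nutrition clinic and describe the change as uncontrolled. The flag removes one source of bias; it does not replace a control group.

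The cost is one tick-box per draw, one analysis rule, and the loss of a few marker values from the unflagged analysis. No extra blood is needed, and enrolment and the perceived-stress analysis stay as they are.

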### **Outcome Measures**

#### **Primary Outcome Measures**

- Target parameter for the primary hypothesis is subjective stress perception (PSS score)

#### **Secondary Outcome Measures**

- Scores of the questionnaires on resilience, quality of life, somatic symptoms, personality structure
- Dietary history: Food Frequency Items
- Patient satisfaction
- Subjective health literacy
- Blood parameters: differential blood count, CRP, IL-6, fasting blood glucose, HOMA index, cholesterol, HDL, LDL, triglycerides, ALT, AST, GGT, creatinine, urea, electrolytes, uric

acid, vitamin D, ferritin, homocysteine, vitamin B12

- Demographic data

## **Methods**

### **Intervention**

Participants receive a link to the questionnaires (via the EvaSys system) at baseline and subsequently at three-month intervals. They are asked to complete them within one week. Standard laboratory tests are also carried out at three-month intervals, but during normal follow-up appointments in the specialized clinic. There is no study-specific blood draw.

